**Ethics and dissemination:**

This study will use secondary data that are anonymised and obtained from studies that have either undergone ethical review or generated data from routine collection systems. Multiple channels will be used in disseminating the findings from this study to academic and non-academic audiences.

Strengths and limitations of this studyThis study will be the first to evaluate the mechanism of the impact of a financial incentive initiative involving Clinical Commissioning Groups (CCGs) to improve antibiotic prescribing in primary care practices in England.The investigation of multiple mediators in this study will help to identify the contributions of multiple strategies in translating the effects of Quality Premium (QP) while unpacking the extent of the effect of specific mediators.Due to the limited data on practice-level interventions or strategies that might potentially mediate the effect of the QP on antibiotic prescribing, we will not be able to extensively investigate the mechanism of QP impact at the practice level.Nevertheless, extensive investigations will be conducted at CCG level where the QP initiative is implemented and rewards paid out.

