### Variables

The predictor will be a binary variable indicating the implementation of the QP intervention. The intervention will include all periods after March 2015 when the 2015/2016 QP guidance in England was published, while the control will be periods prior to this. The primary outcome of interest is the rates of antibiotic prescribing at CCG level in England, which will be a continuous variable indicating the number of items (per STAR-PU) prescribed per month.

To account for differences in practice and CCG characteristics that can contribute to variance in antibiotic prescribing, we will be adjusting for the number of general practitioners in each practice (from the NHS Workforce data),^35^ the index of multiple deprivation (from the Department for Communities and Local Government),^36^ prevalence of comorbidities (asthma, chronic obstructive pulmonary disease, diabetes, cancer, chronic kidney disease (from the NHS Quality and Outcomes Framework database)),^37^ the prescribing rate of other non-antibiotic drugs (opioids and benzodiazepines) and seasonal influenza vaccination rate (from PHE).^38^

Mediator variables will be derived from the questionnaire data from a PHE survey,^39^ with 187 of the 209 AMS leads representing CCGs in England and data from other organisations that have evaluated the interventions treated as potential mediators in this study. In the PHE survey, participants were required to complete questionnaire items, which included their adoption of national and local strategies in their respective CCG to enable them to meet QP targets on antibiotic prescribing in primary care. The mediator variables will be binary or continuous variables, indicating the adoption of key interventions and intermediaries that are hypothesised to reflect in the integration of the QP guidance in improving antibiotic prescribing in primary care practices.

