Using a unified model for the natural direct and indirect effects,^31^ we will investigate the relationship between the QP initiative, the potential mediators and antibiotic prescribing rate with adjustment for the practice and CCG characteristics. This approach addresses the issues associated with the traditional approach to mediation analysis that obtains natural direct and indirect effect estimates through a non-trivial combination of parameter estimates from multiple models for the regression of the mediator and that of the outcome.^32 43^ Also, the unified model is applicable to nonlinear regressions, different measurement types for outcome and mediator variables, and allows for interaction between the exposure and the mediator.^31^

We will first fit single-mediator models with each mediator separately modelled using the *medeff* function in Stata.^44^ With the single-mediator models, we will be able to establish the individual influence of each potential-mediator variable. Variables that showed a mediating effect in the single-mediator models will be added to build a multiple-mediator model using a sequential mediation analysis method.^45^

A sequential multiple-mediator analysis is preferred to merely summing the effects of the single mediators because the sum may differ from the joint mediated effect, particularly as our potential mediators may influence one another.^45^ Modelling all the significant mediators together provides a more accurate assessment of the mediation effects and causal relationship,^46 47^ while assessing the indirect effect of a group of mediators in explaining how and why the intervention impacts on the outcome. The ordering of the mediators in the sequential mediation analysis will be based on evidence from the literature and the outcome of our stakeholders’ workshop designed to identify possible pathways between the predictor, mediators and outcome. The workshop that will validate our conceptual model will also enable us to identify what mediators affect one another and inform interactions to include in our model. All analysis will be conducted in the Stata statistical package V.15.1.

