## Discussion

Although the QP intervention has been reported to have been effective in reducing antibiotic prescribing,^22^ there remain important gaps in the evidence base for this intervention, especially in relation to its mechanism of impact. This study will be the first to evaluate the mechanism of the impact of a financial incentive initiative involving CCGs to improve antibiotic prescribing in primary care practices in England. If our study identifies some key mediators, like other interventions implemented in similar time or in response to the QP initiative, that explain the indirect effect of the QP intervention on antibiotic prescribing, this will provide important evidence on the effectiveness of the implementation of a package of interventions on antibiotic prescribing. The investigation of multiple mediators in this study will also help to highlight the contributions of multiple factors in translating the effects of QP while unpacking the extent of the effect of specific mediators.

Evidence on the mechanism of impact of strategies like QP will be important in improving its uptake and sustainability while maximising its potential in reducing antibiotic prescribing in primary care settings.

Finally, financially incentivised strategies for clinical compliance have been criticised for their ability to result in unintended consequences.^51^ In the case of the QP initiative, unintended consequences like not prescribing antibiotics in cases where they are indicated are possible. However, some of the QP response strategies that we hypothesised as potential mediators (such as prescribers’ AMS education/training) have the ability to mitigate this unintended consequence. By comparing the prescribing rate before and after the QP initiative and identifying the strategies that explain its effect, we will generate evidence that will be important in considerations of the future of this intervention and revisions that may help reduce potential unintended consequences.

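### Mediator-specific shares from the sequential model depend on a mediator order that nothing described lets the data confirm, and no alternative order is planned as a check

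*Protocol article*

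**What the plan says.** The Statistical analysis section of the protocol article describes two steps.

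- **Single-mediator models come first.** The text says: "With the single-mediator models, we will be able to establish the individual influence of each potential-mediator variable".
- **A sequential multiple-mediator model follows**, built from the mediators that showed an effect in the first step. The reason given is that "the sum may differ from the joint mediated effect, particularly as our potential mediators may influence one another". The model is also described as "assessing the indirect effect of a group of mediators in explaining how and why the intervention impacts on the outcome", and as more accurate than the single-mediator results. On order: "The ordering of the mediators in the sequential mediation analysis will be based on evidence from the literature and the outcome of our" stakeholder workshop. The workshop is to identify possible pathways, which mediators affect one another, and which interactions to include.

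The Discussion says that investigating multiple mediators will "help to highlight the contributions of multiple factors in translating the effects of QP while unpacking the extent of the effect of specific mediators". The strengths list after the abstract makes the same promise.

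The mediators come from a PHE survey, "with 187 of the 209 AMS leads representing CCGs in England and data from other organisations that have evaluated the interventions". The Variables section says the survey recorded adoption of strategies. It neither mentions nor excludes adoption dates.

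The planned sensitivity analyses are complete cases (Handling missing data), and shifted implementation dates, a binary outcome and subgroups (Sensitivity analyses). None varies the mediator order. The Limitations section names sequential ignorability, exchangeability and unmeasured confounding, but not order.

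**The concern.** When dependent mediators are entered in sequence, the first is credited with its own path plus what it shares with the later ones. Each later mediator receives only the increment. Reversing the order moves the shared part from one mediator to the other.

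The plan's own reason for using a sequential model is that dependence is expected. The Introduction also points that way: the TARGET toolkit contains audit tools and training resources, while TARGET, auditing and education are listed as separate mediators.

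At stake is the message about which strategies carried the QP effect. An interval computed under one order contains no uncertainty about the order, so a reader of the results could not see how far a share rests on that choice.

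**Working it through.** The plan states no figure here, so there is nothing to reproduce. The check has three parts, and every effect size and correlation in it is assumed.

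**1. Two correlated mediators, closed form.** Take a linear model in which QP raises M1 and M2 by 1 each, residual SDs are 1 with residual correlation rho, and the effects on the outcome are b1 and b2. A mediator's share is the drop in the QP coefficient when it is entered.

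- M1 entered first: b1 + b2 × rho
- M2 entered second: b2 × (1 − rho)
- Sum: b1 + b2 in either order

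With b1 = b2, the first mediator's share is (1 + rho)/2 and the second's is (1 − rho)/2.

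| rho | share if first | share if second |
|---|---|---|
| 0 | 50% | 50% |
| 0.3 | 65% | 35% |
| 0.5 | 75% | 25% |
| 0.7 | 85% | 15% |

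With b1 = 1, b2 = 0.5 and rho = 0.5, the joint effect is 1.5. M1 first gives (1 + 0.25)/1.5 = 83%. M1 second gives 1 × 0.5/1.5 = 33%, leaving M2 with 67%. The ranking reverses.

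**2. One mediator acting on the other, simulation.** There were 400,000 units, with QP to each mediator 0.5, each mediator to outcome −0.3, direct effect −0.1, unit residual SDs, and a path d from M1 to M2.

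| d | M1 share, M1 first | M1 share, M1 second | joint effect, both orders | sum of single-mediator effects / joint |
|---|---|---|---|---|
| 0 | 50% | 50% | −0.300 | 1.00 |
| 0.2 | 54% | 35% | −0.329 | 1.20 |
| 0.4 | 58% | 21% | −0.359 | 1.37 |
| 0.6 | 62% | 11% | −0.388 | 1.50 |
| 0.8 | 64% | 4% | −0.425 | 1.60 |

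As d goes from 0.2 to 0.8, reversal lowers M1's share by 19 to 60 percentage points. At d = 0 nothing moves. The joint and direct effects are the same in both orders. The single-mediator effects do not depend on order, but for d of 0.2 or more they add to more than the joint effect.

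**3. Can the data choose the order?** The survey covers 187/209 = 89.5% of CCGs. In 2 × 187 = 374 simulated units with both mediators measured at the same time, the M1-to-M2 and M2-to-M1 models had the same log-likelihood, −1060.854. Concurrent adoption data of that kind cannot choose between the two orders. Information on timing could help, but the article describes none for the survey items.

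**The case against.** The strongest reply is that ordering mediators from theory and expert input is the normal way to specify a sequential model. That is right, and the ordering rule itself is not the fault. If one mediator truly causes another, crediting the downstream path to the upstream one is the intended effect, and the reversed order is simply a wrong model. That also stands, but it presupposes that the direction is known, and the plan leaves the direction to a workshop.

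It can also be said that the sequential model is aimed at the group effect and that individual influence is assigned to the single-mediator models. This narrows the point. It does not remove it, because the single-mediator estimates overlap when mediators are dependent, and the plan itself calls the joint model the more accurate one.

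The sequential method is specified only by citation, so whether and how the joint effect will be split is not visible. The point therefore applies to any share that is taken from that model. The Limitations section already concedes that causal inference is limited, but its caveat does not name order. An article may leave detail to a fuller plan. Here, however, it states the ordering rule, the sensitivity list and the promise about specific mediators, and the list does not support the promise.

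Two stronger readings are tempting:

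- **The survey cannot verify the order.** The article is silent on adoption dates, other organisations also supply mediator data, and the Chief Medical Officer's letter has a stated first use in September 2014. Silence supports only the statement that nothing described lets the data confirm the order.
- **The strategies tend to be adopted together.** The article does not say this. It says only that the mediators may influence one another.

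**Conclusion.** The point holds in a limited form. Mediator-specific shares from the sequential model depend on the order when mediators are dependent, and the plan neither checks other orders nor attaches a caveat to its promise about specific mediators. The joint indirect, direct and total effects do not depend on order, so a reader should not infer that the mediation analysis as a whole does, or that every mediator-specific result does.

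The illustrated size, a share of 65% to 85% if first against 35% to 15% if second, rests on linearity, two mediators, equal QP effects, equal outcome effects and a residual correlation of 0.3 to 0.7. The documents give none of these values and allow binary mediators. With no dependence the movement is zero. This is a worthwhile, cheap improvement and not a flaw that invalidates the analysis.

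**What to change.** 1. Fix the primary mediator order, with its justification, before the outcome analysis is run.
2. Make the joint indirect effect of the mediators in the model the headline result of the multiple-mediator analysis.
3. Add to the Sensitivity analyses section a refit of the sequential model under the other orders that the workshop considers plausible.
4. Report each mediator's contribution under the primary order together with its range over those orders, beside the single-mediator estimates, and note that the latter overlap.

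The cost is a few reruns of the same model and a short addition to the text. Claims about specific mediators will be weaker where the order matters.

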### Sensitivity analyses

Sensitivity analyses using dummy implementation dates of 1 to 3 months before and after the actual month each of the QP guidance were published will be conducted to assess the difference between the time the guidance is published and the dissemination of information and development of local arrangements by the CCGs. These analyses will further help to investigate the anticipatory effect of the policy and whether lag in implementation attenuates the effect of the intervention.

Also, we will conduct separate analysis with the outcome variable (antibiotic prescribing rate) as a binary variable (indicating whether each CCG achieved the required rate of reduction in antibiotic prescribing as stated in the QP guidance for each year) to examine whether the classification of the outcome variable based on achievement of QP target influences the results.

Subgroup analyses will be conducted on clusters of primary care practices based on their antibiotic prescribing behaviour (high and low prescribers) and indices of deprivation to examine whether any effect of the QP initiative seen in the overall population is different in subgroups of practices. The top and bottom 20% antibiotic prescribers as of March 2015 will be categorised as high and low prescribers. To address the issue of regression to mean in subgroup analyses, we will build a separate model with categorisation into high and low prescribers based on the mean of the prescribing rate of practices in the last 3 months to March 2015. The use of mean of multiple measures will offer a better estimate of each practice’s true mean before the 2015/2016 QP initiative.^48^ The subgroup analysis based on the indices of deprivation data^36 49^ at primary-care practice level will be important in establishing the equity impact of the QP initiative.

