### Data sources

The study will constitute secondary analyses of antibiotic prescribing data from NHS England covering the period 2013 to 2018. CCGs were established in England in April 2013 following the Health and Social Care Act 2012.^33^ Data on antibiotic prescribing in primary care at CCG level will be sourced from the NHS England Antibiotic Quality Premium Monitoring Dashboard, which is produced by the NHS Business Services Authority (BSA).^34^ Primary Care prescribing data are publicly available from the NHS BSA website. The dataset contains the number of antibiotic items (STAR-PU) prescribed in each CCG from the financial year 2015/2016 to 2018/2019, with data for October 2018 the latest at the time of this protocol. Data for the period 2013 to 2015 will be mapped to CCG level from the practice-level data.

Practice-level antibiotic prescribing data will be sourced from OpenPrescribing, an Evidence-Based Medicine DataLab project by the University of Oxford. OpenPrescribing publishes monthly antibiotics prescribing data from August 2013, with data for October 2018 the latest at the time of this protocol. Practice-level antibiotic prescribing data from OpenPrescribing is not STAR-PU weighted, so the extracted data will be STAR-PU weighted using figures from the 2013 Item-based age–sex weighting for oral antibacterials^14^ and the number of registered patients in each age–gender category in a practice for each specific month.

Overall, the dataset offers coverage of at least 3 years postintervention given that antibiotic prescribing became a QP priority in March 2015. This will be important in investigating the immediate direct and indirect effects of the QP initiative while giving an insight into the sustainability of the identified effects (if any) in the long-term.

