### Statistical analysis

Our first analysis will be an interrupted time series to investigate whether antibiotic prescribing rate in England has changed over time, and how such changes, if any, are associated with the QP implementation in March 2015. This will be conducted using the ordinary least square regression method^41^ to assess whether the 2015/2016 QP establishment resulted in a shift in the level and trend in antibiotic prescribing in primary care in England compared with the period before the intervention. Using the practice-level dataset, a univariate time series with the mean antibiotic items (STAR-PU weighted) prescribed in all primary care practices in England for each month will be conducted using the *ITSA* function on Stata, with post-trend specification to show a postintervention trend. The Cumby-Huizinga general test for autocorrelation will be used for general specification test of serial correlation in the time series data.^42^

A new QP guideline was implemented each financial year with changes in the prescribing rate target and the proportion that improved prescribing constituted in the QP award for each year. Our mediation analyses will investigate the effects of the QP by comparing antibiotic prescribing rate in the financial year before its implementation to each subsequent year postimplementation; as such, our dataset for the mediation analyses will have the control group as the financial year before QP and the intervention group as a specific post-QP implementation year. Three analyses will be conducted for each of the three financial years since QP establishment. This will enable us to compare the effects of the different target levels that have been set over the years and the proportions of the QP award attributed to improvement in antibiotic prescribing.

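### Shifting the implementation date by 1 to 3 months does not by itself show anticipation or lag, because the months after March 2015 stay in every fit

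*Protocol article*

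**What the plan says.** The Variables section sets the exposure: "The intervention will include all periods after March 2015 when the 2015/2016 QP guidance in England was published". The Statistical analysis section plans a segmented least-squares model for "a shift in the level and trend in antibiotic prescribing in primary care in England compared with the period before the intervention". The monthly practice-level series is described in Data sources: "OpenPrescribing publishes monthly antibiotics prescribing data from August 2013, with data for October 2018 the latest at the time of this protocol".

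The Sensitivity analyses section then plans "Sensitivity analyses using dummy implementation dates of 1 to 3 months before and after the actual month each of the QP guidance were published". Their first stated aim is to allow for the time between publication of the guidance and local set-up by the CCGs. The second is: "These analyses will further help to investigate the anticipatory effect of the policy and whether lag in implementation attenuates the effect of the intervention".

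The article does not say that an early dummy date is fitted only to data ending before the real date, or that a phase-in window is left out. It does not say how results at the different dates are to be compared. The Limitations section does not raise the point.

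For the mediation analyses the contrast is "the control group as the financial year before QP and the intervention group as a specific post-QP implementation year". The article does not say whether the shifted dates also redefine those years.

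**The concern.** Moving the break relabels a few months and changes nothing else. An early date counts up to three unexposed months as exposed; a late date counts up to three exposed months as control. The true change remains in the data each time, so most of it should reappear at whatever date is tried.

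A fall dated one to three months before publication could then be read as CCGs acting in anticipation when nothing happened early. Estimates that shrink as the date moves later could be read as information about lag when they come from exposed months in the pre-period. If local arrangements were built up gradually, the main level estimate is diluted, and it matters whether the planned check can show by how much.

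**Working it through.** **Inputs.** August 2013 to October 2018 is 63 months (Data sources). With April 2015 as the first exposed month (Variables) there are 20 pre and 43 post months. The model has an intercept, pre-trend, level change and trend change (Statistical analysis). Dummy dates are -3 to +3 months (Sensitivity analyses). The article gives no figure for these analyses, so there is none to reproduce. The step size is my assumption: 4% where a unit is needed. The percentages of the true step do not depend on it.

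**1. Clean step at April 2015, no noise, no anticipation, no lag.** With level and trend both free, the model is two separate straight lines, so the end cases can be checked by hand.

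*Three months early.* The pre-line is flat at zero. The post-segment has m = 46 months, the first three still at zero. With mean time 22.5 and Sxx = 46 × (46² − 1)/12 = 8107.5, those three months take 3/46 + 22.5 × (22.5 + 21.5 + 20.5)/8107.5 = 0.065 + 0.179 = 0.244 off the fitted start. The level change is 1 − 0.244 = 0.756 of the truth.

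*Three months late.* The pre-segment has 23 months, the last three already stepped down. With mean time 11 and Sxx = 23 × (23² − 1)/12 = 1012, the pre-line carried to the dummy date has already moved 3/23 + 12 × (9 + 10 + 11)/1012 = 0.130 + 0.356 = 0.486 of the step. The level change is 1 − 0.486 = 0.514. The false pre-trend is 30/1012 = 0.0296 of the step per month; × 12 × 4% = 1.4% per year.

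All dates, for a 4% fall:

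| Dummy date (months) | Level change (%) | Share of truth | False pre-trend (% per year) |
|---|---|---|---|
| -3 | -3.02 | 76% | 0 |
| -2 | -3.32 | 83% | 0 |
| -1 | -3.65 | 91% | 0 |
| 0 | -4.00 | 100% | 0 |
| +1 | -3.24 | 81% | -0.6 |
| +2 | -2.60 | 65% | -1.1 |
| +3 | -2.06 | 51% | -1.4 |

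Taking March 2015 as the first exposed month gives 76, 83, 91, 80, 63 and 49%.

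**2. With noise.** The residual SD is not given, so the step was set to 1, 2 or 3 residual SDs with independent errors (3,000 simulated series per setting, clean step at the real date). The six dummy dates gave a nominally significant fall in 15-36%, 44-87% and 74-100% of runs respectively; the real date gave 42%, 94% and 100%.

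**3. What the profile across dates shows** (level change in %, noise-free):

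| True change | at -3 | at 0 | at +3 |
|---|---|---|---|
| Clean step | -3.0 | -4.0 | -2.1 |
| Step 3 months late | -2.1 | -3.0 | -4.0 |
| Step 3 months early | -4.0 | -1.8 | -0.5 |

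The residual sum of squares is zero only at the true date. With noise, the best-fitting of the seven dates is the true one in 31-48% of runs at 1 SD, 62-78% at 2 SD and 83-91% at 3 SD; chance is 1/7 = 14%.

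**4. Gradual roll-out** (equal monthly increments from April 2015 to -4%, noise-free). A three-month ramp gives -3.64 at the real date, -3.62 at +1 and less elsewhere. A six-month ramp gives -3.14 at the real date and at best -3.28. Leaving the roll-out window out of both segments (April-June and April-September 2015 respectively) returns -4.00. That exclusion also returns -4.00 for a clean step and for a step three months late, where the main model gives -2.96.

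**5. Precision of the alternatives** (SE of the level change in residual SDs, independent errors). The full fit gives 0.55. With the phase-in window excluded and the change read at April 2015 it is 0.58 (three months) or 0.62 (six months). A placebo break at December 2014 to February 2015, on the 20 months to March 2015, leaves 4, 3 or 2 months after the break. Its SE is 0.99-1.11 with level and trend, and about 0.8 at the lowest with level only.

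**6. Mediation contrast, if the dates are shifted there.** For 12 against 12 months a clean step is recovered at 1 − |d|/12: 92, 83 and 75% for shifts of 1, 2 and 3 months.

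**The case against.** The strongest reply is that the six shifted dates are meant to be read against the real one, and that this comparison is informative. For an abrupt change that stands: the estimate peaks and the fit is best at the true date, and if the effect starts three months late the planned +3 date returns the full -4.0. A reader might infer from the clean-step table that the dummy dates cannot test anticipation or lag at all, or that no planned check could recover a delayed effect. The calculations do not support either reading.

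It is also fair that the article says only that the analyses help to investigate these questions. It does not declare an early effect to be anticipation, and a comparison rule may stand in a fuller plan that is not shown. The mediation point is conditional for the same reason.

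The reply is weaker in two places. When the step is about one residual SD, the best-fitting date is the true one in fewer than half of runs. And the article's own rationale, time for dissemination and local arrangements, suggests gradual uptake. There the size profile can mislead (the three-month ramp peaks at the real date) and no date gives the full effect.

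Replacing the dummy dates with a pre-period placebo would not be sound. That test rests on two to four months after the break, and at February level and trend fit two points exactly. It also addresses only the 2015 guidance, whereas the planned dates cover each year's.

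**Conclusion.** The concern holds in a limited form. Taken one at a time, the shifted-date results do not separate anticipation or lag from a clean step: each returns about 51-91% of the true level change (49-91% if March 2015 is the first exposed month), and late dates add a false pre-trend. Taken together as a profile, they can locate an abrupt change that is large against the noise. They do not recover the size of a gradual one: at most -3.6 (three-month ramp) or -3.3 (six-month ramp) against a true -4.

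These figures rest on an assumed step or linear ramp. The noise results assume independent errors at 1 to 3 residual SDs, and seasonality and autocorrelation were not modelled. This affects how sensitivity analyses are read; the planned main estimates are computed as before. It is worth changing because the remedy is cheap and the misreading is easy.

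**What to change.** In Sensitivity analyses:

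- Keep the dummy dates, but state that they will be read only as a profile, comparing the level estimate and the residual fit across all seven dates, and not as separate tests.
- For lag, add a fit that leaves April-June 2015 out of both segments, with the pre-period ending in March 2015, and a wider version leaving out April-September 2015.
- For anticipation, add a placebo break fitted only to data up to March 2015. Report it as low-precision and supportive: with an SE of about 0.8-1.1 residual SDs, a null result says little.
- If the shifted dates are applied to the mediation contrasts, keep months after March 2015 out of the control year.

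The cost is a change of wording and a few reruns on data already planned for use. The phase-in versions drop 3 to 6 months and widen the interval slightly (SE 0.58-0.62 against 0.55 residual SDs).
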